**2. 1 What is the problem to be addressed. 2.11 Winter respiratory tract infections (RTIs) and influenza.**

Influenza and other respiratory viruses result in overstretched primary care services, and also hospital bed shortages due to the cardiovascular and respiratory complications, especially when viruses causing influenza like illness (ILI) circulate in the community. Minimising the spread of respiratory infections could have considerable benefit for both patients and the health service.

**2.12 Pandemic flu.** The main reservoir of influenza virus is the bird population. Pandemic flu occurs when a new virulent strain develops which is transmissible between humans, and where the human population has little or no prior immunity. The last pandemic was in 1968, and a pandemic is expected - the longest inter-pandemic gap previously was 39 years. Given the capacity of the highly pathogenic H5N1 virus to adapt and change, the next pandemic could be a transmissible virus developed from the H5N1 virus, and if the morbidity and mortality pattern are similar (currently mortality 40%), then the impact on health and society could be potentially significantly worse than the 1918 pandemic. Interventions to minimise spread of influenza could potentially help modify the pandemic curve and help maintain the viability of health and other public services. There has been widespread concern in the public and the media, increased interest in the uptake of influenza vaccine, and expressed anxiety and helplessness (<http://news.bbc.co.uk/1/hi/health/4341496.stm>). Although providing advice on personal protective measures to take could provide an important means of relieving public anxiety, research on compliance with protective measures during the SARS outbreak indicates that scepticism about protective measures is common and advice will only be seen as credible - and therefore effective in changing behaviour and relieving anxiety - if it is evidence-based.

**2.13. Making the diagnosis in ILI: spectrum bias, population behaviour.** A systematic review identified the three-fold combination of the presence of fever, cough and acute onset to be the most predictive clinical features of laboratory diagnosed influenza when influenza virus is circulating in the community. The probability of influenza infection also increases with increasing fever. The assumption is generally made that during a pandemic the positive predictive value (PPV) of a clinical diagnosis will increase; however one of the major unknowns is estimating what is likely to happen to the PPV when people who would not normally contact the doctor then do contact the doctor - as is likely to happen with widespread anxiety in a pandemic situation. This would be expected to reduce the PPV, as has been explicitly acknowledged in the Department of Health guidelines for the management of pandemic flu. It may be that by using 'harder' clinical signs (such as the level of fever) the predictive value can be maintained even when such 'spectrum' changes occur due to the behaviour of the public. Equally if patients contact health providers very early in the illness as patients are being encouraged to, and is in any case likely in a pandemic (e.g. the first 12-24 hours compared to 24-48 hours) the predictive values of symptoms may change. Since in this trial we will be documenting what viruses are circulating, this information will also allow us to perform a nested diagnostic study to estimate the PPV (crucial for the targeting of treatment) and also the NPV (crucial for reassuring patients that they do not have flu if they are being denied treatment) according to such potential 'spectrum' changes. This information will be useful both in inter-pandemic years as public behaviour changes in response to heightened anxiety about influenza, and also in a pandemic.

**2.14 Limiting transmission of influenza and other respiratory infections.** Infection control and the behaviours related to infection control are one of the priorities in the influenza research call by the MRC. The policy of providing anti-virals early (within 48 hours) to patients with ILI in a pandemic is already in place as part of the DOH clinical guidelines. What is less clear is whether other infection control measures will work. Community based major public health interventions are unlikely to be possible interventions for a trial in a non pandemic situation (e.g. it is unlikely patients would be prepared to wear masks in public or modify travel/shopping/leisure arrangements, school closure is not possible etc). Similarly, intensive behavioural interventions (e.g. multiple counselling session) would not be feasible in any pandemic. However, a simple low technology home/family based intervention that could be used in a pandemic is feasible, but could also be assessed - and prove useful - in non pandemic years.

**Method of transmission and infection control.** Influenza is predominantly transmitted by large droplets (particularly within three feet of the infected person), by touching contaminated surfaces (where the virus can be viable for some time) then touching nose mouth or eyes, and by fomites. These patterns of transmission are common to many other respiratory viruses, although viruses vary somewhat in the importance of the different routes of transmission. The use of masks, handwashing, washing down surfaces and cough hygiene have all been recommended in health care settings and the community. For masks there is little specific information for influenza; some evidence from the SARS outbreak suggested a dose response relationship between mask wearing and transmission, but the retrospective design makes firm conclusions difficult. Cough hygiene in the index case (covering mouth when coughing, using disposable tissues) has been recommended, as is staying away from the patient by at least 3 feet - given the evidence of greatest risk being in the immediate proximity of the

case, but there again there have not been adequate trials to test this approach. Although there are issues of generalisability, handwashing with soap or with an alcohol cleanser has the best evidence and is likely to limit transmission of respiratory infections in both adults and children; most controlled studies identified have been positive (see section 2.4) and a review of case-control studies during the SARS outbreak also suggested handwashing may have been protective. Other measures which may be effective include washing down surfaces using a household disinfectant, the use of a separate bedroom/living area where feasible, and separate towels.

**Why this study?** This study addresses key issues in the clinical research agenda (infection control; diagnosis) and provides methodological interest in three areas: a) using a clear theoretical framework to develop a low cost novel intervention (a web-based intervention - which is rare in primary care) b) using novel, predominantly postal recruitment methods, for large patient cohorts c) assess spectrum bias in the diagnosis of community infections.

## **2.2 What are the principal research questions to be addressed?**

1) To develop, then estimate the effectiveness and cost-effectiveness, of a website-based, theoretically-derived, infection control intervention

2) To estimate the positive and negative predictive values of clinical symptoms and signs for laboratory confirmed influenza according to different spectrums of disease defined by consultation behaviour and prior illness duration

**2.3 Why is a trial needed now?** Since current advice on infection control is based on relatively limited trial evidence, a trial of the effectiveness of personal infection control is necessary and timely. There is little understanding of the attitudes, beliefs and anxieties of the public regarding influenza transmission and infection control, and little evidence about how the impact of diagnostic spectrum bias might be minimised. This is particularly important given high levels of public concern regarding influenza, and its prevention. In a short time frame (18 months) this study will develop a low cost technology (an interactive website), which will use a theory-based tailored approach to advice, and which could rapidly be made available should a pandemic strike. Following the development phase we propose trialling the effect of the website. This study will also provide very useful outputs for non pandemic years: it will provide evidence about the effectiveness and cost-effectiveness of a simple and inexpensive intervention for respiratory tract infections and influenza - which are the commonest illnesses in the population - and inform the issues surrounding spectrum bias in the diagnosis of flu-like-illness.

**2.4 Relevant systematic reviews.** We have searched the Cochrane data base, Medline, Embase, Psyclit, and also Google Scholar, using the terms respiratory tract infection, masks, infection control, handwashing, booklets, pamphlets, and influenza which we have reviewed above (Section 2.14). Regarding evidence specific for the transmission of RTIs the WHO writing group have reviewed the existing controlled studies for hand washing: of the 9 studies comparing intervention with a control (one was a historical control) 8 out of the 9 studies reported positive results (ranging from a 10%-50% reduction in infections). However, there are generalisability issues regarding the setting of interventions (health system; social context; site of intervention), and little research specific to influenza nor for other respiratory infections managed in families. We have also performed a broader Cochrane systematic review of the literature on the use of information (booklets, leaflets, and interactive websites/computer programmes) for the management of respiratory infections and other normally self limiting illness (as part of an MRC studentship for [name]). Our review found that 4 out of 6 studies that simply mailed the intervention by post found significant differences in consultation behaviour; the only study that used a health diary similar to the one proposed in our study reported a 15% absolute difference in self treatment behaviours with a mailed booklet (36% vs 51%). The pamphlet we developed for predominantly respiratory illness – which had no clear theoretical framework - was nevertheless surprisingly effective in modifying consultation behaviour for respiratory infections (OR 0.83, NNT 25), and even more effective for those that had consulted previously for respiratory infections. We have also achieved similar changes in behaviours with other booklets; and have recently developed successful structured theoretically based booklets for exercise and for self-management of attacks of vertigo. There is some evidence that the effectiveness of previous infection control interventions in pandemic and non-pandemic contexts may have been limited by variable levels of compliance. While compliance rises with anxiety during a pandemic, it can also be increased by interventions that use psychological theory to identify and address the beliefs, concerns and behavioural practices that influence adherence behaviour. To date we have found no booklets nor website for respiratory infections that have had theoretical development. Rigorously developed information provision for infection control in the form of an interactive website, backed up by regular automated email prompts, addressing an illness that has high public interest, and targeted to allow for individualised advice should be rather more effective in non pandemic years than our previous booklets; furthermore such an intervention is likely to be still more effective for a pandemic.

## **2.5 How will the proposed trial differ from of complement planned, ongoing or recently completed trials?**

We are not aware of any interactive websites for control of respiratory infections, and no ongoing trials.

## **2.6 How will the results of this trial be used? This study will provide:**

**In phase I (development and piloting) :** a) Information regarding the attitudes, beliefs and anxieties regarding influenza and its transmission both for pandemic and inter-pandemic years; b) a low cost simple technology (an

interactive website) which could reduce public anxiety and improve patients' attitudes, intentions and enablement regarding managing and preventing influenza and other respiratory infections within families; the intervention will be made available immediately should a pandemic occur; even with modest effectiveness the intervention is likely to be highly cost-effective, and rapidly and widely available to most of the UK population;

**In Phase II (the main trial) . This study will:** a) assess whether a simple strategy to control infections in families is likely to be effective in non-pandemic years - the intervention will be available at the end of the trial for the whole UK population; such an intervention could potentially make an important difference if and when a pandemic influenza does occur, as compliance is likely to be higher in a pandemic situation. b) A virological sub-study will provide important information about the pattern of viruses circulating during the trial period to inform generalisability of the intervention; it will also inform early diagnosis and treatment of flu-like-illness; assess the likely magnitude of diagnostic spectrum effects if the consultation behaviour of the public changes; and provide some information about how robust individual symptoms and signs are to spectrum bias.

**2.7 Safety of patients.** There are no safety issues in this trial

### **3.1 Proposed trial.**

**Development phase (12-18 months).** We will a) perform qualitative and survey work to determine the key concerns, beliefs and attitudes related to influenza, pandemic influenza, and infection control behaviour

**Trial phase: Pilot trial.** We will first pilot the intervention and outcome measures.

#### **Main trial:**

Adult patients (aged 18+) living with at least one other person. Patients whose GP notes show a skin problem that may affect handwashing ability, and those who live in households where no one else is willing to provide illness feedback will be excluded. Participants will be randomised to:

- 1) Access to an interactive website by a personal password, providing tailored advice; this will be reinforced by email prompts and reminders to use the website; patients will be advised to use hand-washing and a range of infection control measures both within and outside the family
- 2) Normal care (access to the website at the end of the trial)

**Outcomes:** transmission of ILI and other infections between family members, severity and duration of ILI and other respiratory infections.

**Virological sub study:** based on laboratory confirmed virological diagnosis, we will document the nature of circulating viruses, estimate whether transmission differs according to the type of viral illness; provide estimates of the predictive value of clinical symptoms and signs according to the spectrum of illness (defined by contact with the NHS and prior duration of illness).

**3.2 What is the proposed trial design.** An RCT, with a development phase and a nested viral study.

### **3.3 What are the planned trial interventions.**

**Infection control website.** Our key intervention will be access with a personal password to a website providing advice on infection control behaviours, with reinforcement by email reminders to use the site. A website is likely to be the most efficient and cost-effective mode of delivery in a pandemic as the majority of homes now have access to the web and the figure rises each year (National Statistics; August 2006); currently more than 60% of households have access to the web and the figure goes up year on year by 5% each year in a linear fashion - which suggests that even by the end of this trial 80-90% of families could have home access to the web. A recent US study confirmed that most people would use Google as their first source of information in a pandemic. A website will facilitate tailoring of the intervention to the individual, and personalised action planning - and thus is the most likely to be effective. Having both personalised advice via the web and behavioural prompts (regular email contacts) will provide mutual reinforcement of consistent messages. The website will be tailored to provide targeted advice based on the factors that have been shown to be important influences on behaviour in the qualitative study and survey carried out in the development phase. These are likely to include: family circumstances and lifestyle factors that may affect which behaviours are feasible and preferred (e.g. availability of suitable space to isolate infected family members, skincare problems); beliefs and concerns regarding infection transmission and control; strategies for overcoming barriers to adherence (e.g. forgetting, negotiation with other family members); current infection status of family and adherence levels (i.e. specific advice will be given when the individual or another member of the family is ill, and depending on the current level of reported adherence to each behaviour). The randomised individual (the index person) will be the main target for behaviour change which should limit spread from that person to members of the household and vice versa. However the maximum effect on illness in the family will be if all members of the household participate and change behaviour; this will be encouraged at invitation, and all members of the household will be encouraged to use the website. The extent to which it is possible to engage other members of the household, and the optimum methods for achieving this will be explored in the development phase. During the pilot, participants will be made aware that they will not be able to participate if all other members of their household refuse to provide additional information on their cold and flu illnesses. Through the website and the individual passwords

we will be able to monitor whether patients have used the website, and how often. Patients who have not used the website will be prompted by email to use the site. Following accessing of the website we will generate regular automated emails at monthly intervals as a reminder to use the website; these reminders will enable us to monitor compliance in the intervention group and give targeted advice. We will provide further email prompts to all patients when influenza virus has started circulating in the community. During the development and pilot phase we will examine the acceptability and feasibility of using the website as the main method of interacting with patients for the whole trial process (including outcome data collection), with paper-based reminders only when web-based measures are not completed. In the development phase we will also explore the need to provide supplies of some materials to help in infection control (a handgel dispenser sufficient to cover periods of respiratory illness).

**Target behaviours.** The intervention will encourage the use of regular handwashing throughout the winter months using normal soap or alcohol based handgel both within the family and in other settings. Then when somebody in the household has developed an ILI or other RTI (defined below), the aim is to influence the following behaviours: 'hygiene' in the index case and among family members- handwashing with soap or alcohol gel before any food eaten and after any skin or clothes contact with index case; three times daily washing of kitchen work/dining surfaces using a normal household cleaner; covering mouth when coughing (also see mask wearing, but mask wearing in non-pandemic years may not be acceptable or possible); minimising skin contact with family members, using disposable tissues, using separate towels and physical distancing where possible (more than 3 ft distance; minimising time in the same room; living/sleeping in separate rooms/bedrooms where possible). Wearing masks by the patient and family when in the same room as those with influenza (using FFP2, FFP3, N95 or equivalent masks) may limit the spread of large droplets by coughing; but it is the least likely behaviour to be acceptable in inter-pandemic years; our qualitative study will indicate how acceptable mask wearing is likely to be and inform whether masks are provided in the main trial. Based on the literature to date the key behaviour which has the most evidence is handwashing, and so this will be emphasised, but the website will help patients to develop individualised action plans based on their circumstances. Although a development phase cannot realistically determine with any power the effectiveness of each component of behaviour change in modifying transmission, in the analysis of the main trial we will be able to explore this. A development phase will nevertheless be able to provide some insight into the effectiveness of the different behaviours; development is also necessary for a complex intervention to allow us to understand and model the key factors determining the likely implementation of these behaviours ([http://www.mrc.ac.uk/pdf-mrc\\_cpr.pdf](http://www.mrc.ac.uk/pdf-mrc_cpr.pdf)):

**Theoretical basis.** The behavioural literature and empirical trial data suggest that a tailoring approach that personalises advice to the individual is likely to be most effective in changing attitudes and behaviours. Psychological theory will be used to identify the factors on which advice must be tailored. The Theory of Planned Behaviour will be used as the primary basis for developing the tailored intervention, as there is evidence that components of the model that are amenable to change by intervention are key predictors of health-related behaviour; a meta-analysis of 47 studies also shows that these attitudes/beliefs can be experimentally manipulated and do then change behaviour. We have experience of several successful studies which have used structured booklets based on the Theory of Planned Behaviour combined with traditional behavioural techniques. The Theory of Planned Behaviour identifies the proximal factors influencing behaviour (perceived costs/benefits, others' attitudes, barriers/support). To investigate additional factors that may directly or indirectly influence behaviour it can be useful to draw on more than one theory; for example, the Theory of Planned Behaviour can be usefully supplemented by Self-Regulation Theory and by considering volitional factors influencing the implementation of intentions. We will therefore employ a causal modelling approach to identify additional relevant influences on behaviour and appropriate corresponding methods of intervening to change behaviour. We will use Protection Motivation Theory to look at perceived threat of infection (personal vulnerability, consequences, and fear), since mask-wearing in the SARS epidemic was related to perceived susceptibility to infection as well as perceived benefits of mask-wearing. We will use the Self-Regulatory Model to examine personal models of viral infection (e.g. perceived cause, nature and timeline of infection) that may affect attitudes to infection control (e.g. beliefs that respiratory infection is entirely airborne or occurs too quickly to be prevented), as there is limited evidence that these may have influenced behaviour during the SARS epidemic. We are aware of no theoretical work on factors influencing our target behaviours in the context of nonpandemic respiratory infection. However, based on the literature on behaviour to limit STD transmission we will assume that infection control will require negotiation between the patient and other family members. We will also use evidence-based methods of assisting patients to carry out their intentions regarding preventive behaviour including: a) planning and cueing of behaviour, for example assisting the individual to set their own behavioural 'targets' for different infection control behaviours, and to make an explicit commitment to these targets (a signed list and website record), where possible in collaboration with members of their family; b) identifying situations when lapses may occur, and suggesting coping strategies; c) using a paper or web-based diary to self-monitor the target behaviours during episodes of RTI ( this will automatically trigger reinforcement and advice relevant to self-reported behaviour).

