**Control group (normal care).** As in the intervention group, the control group will have access to the GP/practice in the normal way for respiratory illnesses and ILI (where low levels of antivirals are normally prescribed). We are not proposing to encourage all patients to access antivirals early in the illness, since the effect would be to reduce transmission rates to substantially below the rates that would be expected in a pandemic (where, even with antivirals, transmission rates are likely to be high, given the low levels of immunity and severity and duration of the illness). In our previous RCTs which have randomised at patient level (including RCTs using information leaflets) there has been little or no contamination of the control groups. In this study, since access will only be possible by a personalised password, contamination is even less likely. Inevitably some patients in the control group will want to go searching on the net for their own information, and to some extent by asking patients to participate we may increase their curiosity about such issues. We will minimise the possibility of this contamination by explicitly raising the issue prior to randomisation, and stressing the importance of a fair test of the website; we will ask patients who intend searching the web not to agree to participation; and we will minimise the incentive to do so by offering access to the website to all control patients at the end of the year. We will monitor any contamination of the control group at the end of the year of follow-up by asking all patients whether they have accessed infection control information by the web and assessing levels of key behaviours of all patients at the end of the trial to determine whether these have changed within the family. Possible contamination of the control group raises the issue of dilution of effect size, but our effect sizes are based on past trials where the sort of level of contamination possible (i.e. availability of access to information) was at least as great as in the proposed study; for example our booklet/leaflet study came at a time where the local PCTs were providing mass mailing of information booklets to many PCTs, and the companies supplying booklets were engaged in active advertising locally.

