**3.4 What are the proposed practical arrangements for allocating patients to trial groups?** We propose using a very similar mechanism to our previous leaflet trial, which used a novel method to recruit large numbers of patients. 1500 patients from each practice will be identified by the practice staff with the help of research staff. If the practices would like help (the research staff will hold honorary contracts with the PCT). Letters will be sent to patients inviting them to participate. Assuming conservatively at least 66%-70% agree to the main study (we achieved an 80% uptake previously in a similar study and using a questionnaire burden that was higher than the present study) then 1000-1100 patients in each practice should agree. If fewer agree more letters will be sent out in each practice. Patients willing to participate can return the consent form directly to the research centre, or talk with the research team before replying. Those patients wanting more explanation can also attend sessions run by the practice nurse and/or research staff as appropriate. Patients will then have time to think about the study, and can also subsequently contact the research centre later before sending their consent forms back directly to the research centre. Patients can either return the consent form by post (which has previously been the case for the majority), log on to the website to confirm consent (assuming ethics approve this method). If our pilot study indicates that a primarily postal method of trial administration is needed then the trial nurse will then provide lists of patients' numbers and details in each practice to an external randomisation line (the data will include stratification variables: age >65; influenza vaccination status; size of family, children under aged 16 living at home; access to the internet; willingness of other members of the family to use the website; attendance in the previous year with respiratory infections; a skin complaint that may affect handwashing); the randomisation centre will then randomise, stratified by the above variables, and provide the randomisation lists which will be distributed to the practice staff. The practice staff will then send out separate batches of letters to intervention patients (with the personalised website password depending on which intervention they will access) and to control patients (no password). Patients consenting to the diagnostic study will be given instructions on how to take samples, and will see a nurse for demonstration as necessary. Patients will be given the symptom diary for them to complete when an ILI develops. If the pilot study indicates that a primarily website-based method of trial administration is appropriate then randomisation will be automated and outcome measures collected electronically (with paper-based follow-up of non-respondents).

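### Household behaviour change is to be encouraged in the invitation, before randomisation, so future control households are exposed to it: an avoidable risk of bias towards no difference, of unknown size

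*Protocol*

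**What the plan says.** **Encouragement.** Section 3.3 (Infection control website) states that the largest effect on illness in the family is expected if "all members of the household participate and change behaviour; this will be encouraged at invitation". Encouraging household members to use the website is a separate clause that follows.

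**Order of events.** Section 3.4 begins with the mailing: "Letters will be sent to patients inviting them to participate". Consent forms come back next, and then "the randomisation centre will then randomise, stratified by the above variables". Only after that do separate letters go out, with a password for intervention patients and without one for controls. The stratifiers include "willingness of other members of the family to use the website", so that item is known for both arms before allocation.

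**Control condition.** Section 3.1 (Main trial) gives the second arm as "Normal care (access to the website at the end of the trial"). The same list places email prompts in the first arm.

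**Prompts.** Still under Infection control website, section 3.3 adds: "We will provide further email prompts to all patients when influenza virus has started circulating in the community".

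**Safeguards.** Section 3.3 (Control group) argues that "since access will only be possible by a personalised password, contamination is even less likely". It plans to ask people who intend to search the web not to take part. It states that "our effect sizes are based on past trials where the sort of level of contamination possible" was at least as great as here. At the end of follow-up it will ask about web information and assess key behaviours of all patients.

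**The concern.** An invitation sent before allocation cannot differ by arm. If it encourages households to change behaviour, the people who later become controls have had that encouragement from the trial itself. Any hygiene change that follows would lower transmission among controls and shrink the difference the trial is built to detect. Prompts at the start of the influenza season, if they reach controls, would act when transmission matters most.

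The protocol is careful about this kind of effect elsewhere. Sections 3.9 and 3.10 delay the attitude and behaviour questionnaires to the end of winter so that filling them in does not change control behaviour. Encouraging behaviour change in everyone's invitation sits badly with that. A shift of this kind cannot be repaired in the analysis.

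**Working it through.** **Step 1: can the encouragement be confined to one arm?** Section 3.4 gives the sequence invitation, consent, randomisation, allocation letter. The alternative web-administered route automates randomisation and data collection but does not move the invitation. The pilot text in section 3.3 also lists invitation and intervention as separate items. So whatever the invitation contains reaches both future arms.

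**Step 2: do the safeguards cover this route?**
- The password restricts access to the website, not the content of a letter.
- The request about web searching concerns what patients look for themselves.
- The contamination allowance claimed for the effect size is illustrated by mass-mailed booklets and commercial advertising, which are outside sources. No dilution percentage is given.
- The end-of-trial behaviour assessment does include controls. In sections 3.9 and 3.10, however, the main trial measures these outcomes only at the end of winter and in a random 1 in 20 (16,000 / 20 = 800 patients). With no baseline and the same invitation in both arms, a shared shift could be neither separated nor corrected.

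**Step 3: reproduce the plan's sample size.** Inputs from section 3.12 and its table: 20% vs 16%, two-sided 5%, 80% power, 24% with transmission possible, 20% loss.

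n per group = [1.960 √(2 p̄ q̄) + 0.842 √(p₁q₁ + p₂q₂)]² / (p₁ − p₂)², with p̄ = 0.18

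= [1.960 × 0.5433 + 0.842 × 0.5426]² / 0.04² = 1,447, as stated.

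Total = 2 × 1,447 / (0.24 × 0.80) = 15,073. Rounding up each group first (7,536.5 to 7,537) gives the stated 15,074.

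**Step 4: illustrate dilution at the planned 16,000.** Evaluable per group = 16,000 × 0.24 × 0.80 / 2 = 1,536. Equal allocation is assumed, because the table gives one N per group. Let f be the share of the 4-point effect that controls also obtain. This is an assumption, since the documents give no value.

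Control rate p_C = 0.20 − 0.04 f; intervention rate p_I = 0.16.

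Power = Φ{[(p_C − p_I) √n − 1.960 √(2 p̄ q̄)] / √(p_C q_C + p_I q_I)}

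For f = 10%: (0.036 × 39.19 − 1.960 × 0.5410) / 0.5404 = (1.411 − 1.060) / 0.5404 = 0.649, so power is 74.2%.

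| Assumed f | Control rate | Power at 16,000 | Total N for 80% power |
|---|---|---|---|
| 0 | 20.0% | 82.3% | 15,073 |
| 10% | 19.6% | 74.2% | 18,459 |
| 25% | 19.0% | 59.0% | 26,230 |
| 50% | 18.0% | 31.4% | 57,678 |

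The margin between 15,074 and 16,000 absorbs about 3% dilution before power falls below 80%.

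**The case against.** The strongest case on the other side has five parts.

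- **Content of the invitation.** Its text is not shown, and the tailored advice, action plans and reminders all sit behind the password. The sentence may be mainly about getting households to take part, and section 3.3 leaves the best way of engaging them to the development phase. This stands as a limit on the claim. A reader might infer that controls receive part of the intervention, or that the difference is diluted; the documents show neither. But the sentence names behaviour change as well as participation, so the exposure follows from the wording.
- **The prompts.** The phrase *all patients* follows sentences about website users and non-users and may mean everyone in the website arm, and section 3.1 gives email prompts to that arm only. No hygiene content is stated. This stands: the prompts are ambiguous, not a demonstrated second route. The diagnostic substudy does need a notice that influenza is circulating, but only for patients who agreed to it.
- **Detection.** A reader might infer that the end-of-year check asks only about web information. That is not so; key behaviours are assessed as well. The limits are those in step 2 of the working.
- **Contamination was considered.** The protocol concedes that being asked to take part may raise curiosity, and it claims an allowance in the effect size. That addresses information from elsewhere, not encouragement from the trial.
- **Magnitude and direction.** Nothing supports any particular dilution fraction, and the bias runs towards no difference, so it would not create a false positive. Both points stand.

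**Conclusion.** The concern holds as a design risk. Followed as written, sections 3.3 and 3.4 expose future control households to encouragement to change behaviour before allocation, which conflicts with a normal-care comparator, and no stated safeguard deals with it. The prompt wording may add a second exposure. The bias would be towards no difference and its size is unknown; the power figures show only how little room the design has, under assumed fractions. It would be wrong to conclude that the sample size is miscalculated, since it reproduces, or that the control arm has ceased to be normal care, since that depends on an invitation text that is not available. Because the exposure can be avoided by rewording and cannot be corrected afterwards, the change should be made.

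**What to change.** 1. In sections 3.3 and 3.4, limit the pre-randomisation invitation to neutral content: whether household members would report illnesses, and whether they would use a website if allocated to it. This still supplies the household-willingness stratifier and the eligibility condition in section 3.6.
2. Move encouragement to change behaviour to the post-randomisation password letter, for the intervention arm only.
3. In the section 3.3 sentence on influenza-season prompts, replace *all patients* with *intervention patients*. Where controls need to know that influenza is circulating, for example for the virological substudy, send the same notice to both arms with no hygiene content.

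The cost is rewording the invitation and a few protocol sentences. Household engagement in the intervention arm would start slightly later, at the password letter instead of the invitation. The sample size need not change for this.
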